Before ICBT for pediatric OCD can be recommended for implementation in routine clinical care, it is essential to evaluate whether this approach is comparable or noninferior and cost-effective compared with the gold standard of face-to-face CBT. Even if ICBT were less efficacious than face-to-face CBT, it might still have a meaningful place in the health system, as its potential cost-effectiveness could outweigh its loss of efficacy. In that scenario, ICBT might be used in a stepped care model in which patients are first offered ICBT as a low-intensity intervention, reserving higher-intensity treatments that require specialist input (eg, face-to-face CBT) for more complex patients or those who do not benefit sufficiently from ICBT.^18^ Stepped care approaches are heralded as the ideal model of psychiatric service delivery^1^ but have rarely been evaluated.

We describe the trial protocol of a multicenter, single-blind, randomized clinical noninferiority trial aimed to investigate whether therapist-guided ICBT implemented within a stepped care model is noninferior to, and cost-effective compared with, the gold standard of face-to-face CBT for pediatric OCD. The main hypothesis is that the stepped care ICBT approach will be noninferior to gold-standard treatment (face-to-face CBT) in reducing clinician-rated OCD symptoms and will also be associated with lower resource use. As a secondary aim, the trial will explore whether the outcomes of ICBT differ between clinic-referred and self-referred patients.

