## Methods

### Study Design

The study is a 2-site randomized clinical noninferiority trial for children and adolescents with OCD. Participants randomized to stepped care ICBT first receive ICBT for 16 weeks; patients classed as nonresponders at the 3-month follow-up are offered a course of face-to-face CBT for up to 12 weeks. Participants randomized to the gold standard treatment receive face-to-face CBT for 16 weeks; as in the stepped care group, patients classed as nonresponders at the 3-month follow-up are offered additional sessions of face-to-face CBT for up to 12 weeks. The full trial protocol is available in the Supplement.

The primary end point is 6 months after the end of the first course of treatment (6-month follow-up). Long-term effects will be investigated 1, 2, and 5 years after treatment completion. The trial design is graphically summarized in the Figure.

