### Randomization and Allocation Concealment

The allocation sequence is generated by an independent external party, the Karolinska Trial Alliance (KTA). The research team and the therapists who enroll the participants are not involved in the randomization or allocation process. Participants are randomized to either stepped care ICBT or gold-standard CBT through an online automated system for clinical trials. The allocation ratio is 1:1. Randomization is stratified by source of referral (clinician-referred or self-referred) and participant’s age (children [7-12 years] or adolescents [13-17 years]).

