#### Nonresponders

Participants in either group not meeting strict criteria for clinical response^30^ at the 3-month follow-up are offered up to 12 sessions of face-to-face CBT for OCD.^6^ This additional treatment is delivered between the 3-month and 6-month follow-ups. The content of the treatment is identical to the face-to-face CBT treatment, with the main focus on therapist-guided ERP.^28,29^ Individual adaptations are made to ensure optimal treatment dosage, including longer sessions or home visits as appropriate.

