#### Outcome Data

The only previous pediatric OCD trial using a noninferiority design used −5 points on the primary outcome measure (CY-BOCS) as a noninferiority margin with an SD of 8.^28^ In the present study, we set the noninferiority margin to −4 points to gain greater precision. The noninferiority analysis will be based on the CY-BOCS score at the primary end point (6-month follow-up) and determined by the confidence interval around the mean difference between the 2 groups. The estimated enrollment is 152 participants, which gives an estimated power greater than 95%, allowing for possible data attrition (10% based on experience from our previous trials). The power is estimated based on each participant being observed at 4 points (baseline, after treatment, 3-month follow-up, and 6-month follow-up). We used a linear random intercept model with 1000 bootstrap samples using the following values, which were based on individual-level data from a previous study of therapist-guided ICBT for adolescents with OCD that used 3 repeated observations^14^: intercept (22.45), slope (−0.37 per week), SD of the random effect (4.03), and SD of the residual error (3.94). In other words, if the stepped care ICBT approach is truly noninferior to the gold-standard treatment, 152 patients will give an estimated probability greater than 95% that the upper limit of a 1-sided 95% confidence interval (or, equivalently, a 90% 2-sided confidence interval) will be below the noninferiority limit of 4 points on the CY-BOCS. No specific noninferiority margin is defined for the secondary outcome measures, but we expect no statistically significant difference between the groups on these measures.

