Data will be analyzed according to the participants’ original treatment allocation in line with intention-to-treat principles. Data analysis on the continuous outcome measures will be performed with mixed-effect regression analyses for repeated measures with maximum likelihood estimation. The model will include fixed effects of time, treatment group, and site and an interaction effect of treatment group by time, as well as random intercept and random slope to account for individual differences. In line with our secondary aim, a model with an interaction effect of treatment group, time, and source of referral will be implemented to explore whether source of referral is a moderator of treatment effect. Ordinal data will be analyzed with ordinal regression, binary data will be analyzed with logistic regression, and paired binary data will be analyzed with McNemar tests. Logistic regression will be used to test whether the blinded assessor’s guesses on treatment allocation are better than chance. Within- and between-group effect sizes will be reported as Cohen *d*. If the proportion of missing data is greater than 10%, we will perform multiple imputation with 10 extra data sets.^46^ In a first sensitivity analysis, we will compare the results of the complete-case analysis with those of the multiple-imputed data sets. If the results are inconsistent, we will investigate the reasons of the nonresponse and discuss their possible impact on the study findings. In a second sensitivity analysis, we will exclude the participants who violate protocol (eg, start medication in the middle of the trial) and investigate any inconsistencies with the results from the main analysis. Additional analysis of the 1-year, 2-year, and 5-year follow-up data will evaluate whether the treatment gains are maintained long term.

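### The secondary aim asks whether ICBT outcomes differ by referral source, but the analysis named for it tests whether the between-arm difference varies by referral source

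*Protocol article*

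**What the plan says.** The Introduction of the protocol article gives the secondary aim: "the trial will explore whether the outcomes of ICBT differ between clinic-referred and self-referred patients". The reason appears just before it in the same section. Participants in the earlier ICBT trials were mainly self-referred and may have been a selected group, so it is unclear whether those results carry over to ordinary clinic patients.

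Outcome Data, under Statistical Analysis, presents the analysis as following from that aim: "a model with an interaction effect of treatment group, time, and source of referral will be implemented", with the purpose "to explore whether source of referral is a moderator of treatment effect". It names no contrast within the ICBT arm and does not list the visits used in this model.

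On the additional face-to-face CBT offered to nonresponders in either group, the Nonresponders section says: "This additional treatment is delivered between the 3-month and 6-month follow-ups".

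**The concern.** The aim compares two kinds of patient who receive the same treatment. The named term compares two treatments and asks whether their difference shifts between kinds of patient. The two agree only if referral source makes no difference to outcome under face-to-face CBT.

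The Introduction itself gives a reason to doubt that. It suggests that self-referred participants may be more educated and more motivated, and such traits could help under either treatment. In that case the interaction would be near zero while clinic-referred patients did worse with ICBT. The generalizability question would then have been put to a quantity that cannot show the answer. The reverse can also happen: a referral gap confined to the face-to-face arm gives a nonzero interaction although ICBT outcomes do not differ.

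**Working it through.** **Inputs from the protocol article.** 152 participants allocated 1:1, so 76 per arm; 10% attrition, so 152 × 0.9 / 2 = 68.4 per arm; random-intercept SD 4.03 and residual SD 3.94; margin 4 points; one-sided 5% for noninferiority.

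**Assumptions.** Two-sided 5% for the referral analysis, for which no level is stated. Share self-referred p between 10% and 50%, because no share is given. Equal referral mix and variance in the two arms; randomization is stratified by referral source, which makes the equal mix reasonable.

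**Step 1: the plan's own power.** In a random-intercept model the intercept cancels from a change score, so the change SD is √2 × 3.94 = 5.57. The between-arm SE is 5.57 × √(2/68.4) = 0.953. Power is Φ(4/0.953 − 1.645) = Φ(2.55), about 99.5%. Other forms of the model give 99.4% to 99.8%. The stated power above 95% is reproduced, so these variance components are a fair basis for what follows.

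**Step 2: what each quantity is.** Let A be the self-referred minus clinic-referred difference in mean CY-BOCS change within stepped care, and B the same difference within face-to-face CBT. The aim concerns A. The three-way term at a given visit is A − B. With A = B = 4 points, the term is 0 and the quantity in the aim is 4.

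**Step 3: precision.** With n = 68.4:

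- SE(A) = 5.57 × √(1/(np) + 1/(n(1−p)))
- SE(A − B) = √2 × SE(A)
- Difference detectable at 80% power = (1.960 + 0.842) × SE = 2.80 × SE

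At p = 0.5, SE(A) = 5.57 × √(1/34.2 + 1/34.2) = 1.35 and SE(A − B) = 1.91. Each cell below gives the within-ICBT contrast, then the interaction.

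| Share self-referred (assumed) | SE | Detectable difference, points | Power for 4 points |
|---|---|---|---|
| 50% | 1.35 / 1.91 | 3.8 / 5.3 | 84% / 56% |
| 20% | 1.68 / 2.38 | 4.7 / 6.7 | 66% / 39% |
| 10% | 2.25 / 3.18 | 6.3 / 8.9 | 43% / 24% |

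Under a random-intercept model with categorical time, the change SD is the same at every post-baseline visit, so the table serves posttreatment, 3 months and 6 months alike at that attrition. The planned analysis also has a random slope, for which the article gives no variance. That could raise the SEs, but under the assumptions above the factor √2 remains.

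**Step 4: simulation.** In 4,000 runs with the same 4-point referral gap in both arms and a 50:50 mix, the three-way test rejected in 5.8% of runs, close to its nominal level. The within-ICBT contrast rejected in 84% when taken from the joint model and in 83% when fitted to the ICBT arm alone.

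**The case against.** The strongest reply is that the planned model already contains the answer. Fitted in the usual hierarchical way, it includes the referral-by-time contrast within stepped care, and the simulation recovers that contrast from it. An article may also leave the list of reported contrasts to a fuller document. The first part stands: a reader might infer that the model cannot answer the aim, and that is wrong. The second part does not remove the point. The article is not silent here: it ties this aim to the interaction and to moderation of the treatment effect.

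A moderator analysis on a stratification factor is also a conventional way to ask whether a treatment effect carries over between populations, and the within-arm contrast is not randomized and is open to confounding. Both statements are true. They are reasons to keep the interaction and to label the within-arm contrast honestly, but they do not make the interaction an estimate of what the aim asks.

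Some stronger readings are not supported:

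- That the moderator analysis rests on data from after the additional treatment. Outcome Data lists no visits for this model. The 6-month visit is the primary end point and is probably included, but the model is longitudinal and would also use earlier visits. The article at times calls the whole stepped care arm the ICBT group, and on that reading a 6-month outcome could belong to the aim.
- That the larger SE is itself a fault. It is a property of a different estimand. The table shows how far the two quantities diverge; it does not show that the interaction is poorly designed.
- That precision should be judged with SD 8. Outcome Data quotes that value from an earlier trial, and it is not what this trial's power calculation used.
- That the investigators will read a null interaction as proof of generalizability. Nothing in the article says so.

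**Conclusion.** The named analysis does not target the stated aim. When referral source affects improvement equally in both arms, the interaction is zero whatever the size of the gap in ICBT outcomes. This follows from the definitions and needs no numerical assumption.

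The figures rest on the protocol's random-intercept variance components, 10% attrition, an assumed two-sided 5% level, an assumed self-referred share of 10% to 50%, and equal mix and variance across arms. The 4-point illustration refers to a gap in improvement. A gap already present at baseline and carried forward unchanged would not appear in a change-from-baseline contrast either.

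The aim is secondary and exploratory, which limits the weight of the point. The primary noninferiority comparison and its power are untouched.

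**What to change.** In Outcome Data, name the referral-source difference in CY-BOCS change from baseline within the stepped care arm, with its confidence interval, as the estimate for the secondary aim, taken from the model already planned. Report it at posttreatment and at the 3-month follow-up. Nonresponders are offered face-to-face CBT between 3 and 6 months, so a 6-month contrast would describe the stepped care strategy and not ICBT alone; if it is also shown, say so. Label the contrast observational and exploratory. Keep the three-way interaction as a separate question about moderation of the between-arm effect, and state that a null result there does not answer the aim.

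The cost is a few sentences. No new data, visits or models are needed. A 3-month between-arm noninferiority comparison has no bearing on referral source and is not part of this request.

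### None of the stated sensitivity analyses is reliably conservative for noninferiority, and the missing-data check hangs on a trigger equal to the planned attrition

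*Protocol article*

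**What the plan says.** All of this stands under Statistical Analysis, Outcome Data, in the protocol article.

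- **Main analysis.** "Data will be analyzed according to the participants’ original treatment allocation in line with intention-to-treat principles". The method for continuous outcomes is "mixed-effect regression analyses for repeated measures with maximum likelihood estimation".
- **Imputation trigger.** "If the proportion of missing data is greater than 10%, we will perform multiple imputation with 10 extra data sets".
- **First sensitivity analysis.** "we will compare the results of the complete-case analysis with those of the multiple-imputed data sets". If the two disagree, "we will investigate the reasons of the nonresponse and discuss their possible impact on the study findings".
- **Second sensitivity analysis.** "we will exclude the participants who violate protocol (eg, start medication in the middle of the trial", and then "investigate any inconsistencies with the results from the main analysis".
- **Planned attrition.** The power statement is described as "allowing for possible data attrition (10% based on experience from our previous trials".

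Noninferiority is declared if the upper limit of a one-sided 95% confidence interval for the 6-month CY-BOCS difference lies below 4 points. Below, the difference is stepped care minus face-to-face CBT, so a positive value is worse for stepped care.

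**The concern.** In a noninferiority trial, a bias toward no difference favours the claim. At least one sensitivity analysis should therefore be built to move the estimate against the new treatment.

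The first stated check is not built that way. A maximum-likelihood mixed model already uses every observed visit and is valid if data are missing at random. Standard multiple imputation rests on essentially the same assumption, and a complete-case analysis assumes more. (The article does not name the assumption; it follows from the methods.) Comparing the two cannot reveal what happens if dropouts from stepped care do worse than their earlier scores predict. The check also applies only above a threshold equal to the attrition the trial expects.

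The second check removes patients because of something that happened after randomization and that may mark treatment failure. Participants and therapists are not blinded (Blinding section), so medication starts could differ by arm. If failing patients start medication more often under stepped care, exclusion takes failures out of that arm.

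What is at stake is a reassuring agreement between analyses that would not in fact show robustness.

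**Working it through.** **Inputs from the article.** 152 participants at 1:1, so 76 per arm; margin 4; one-sided 5%; attrition 10%; SD of the random effect 4.03 and of the residual 3.94; SD 8 in the earlier noninferiority trial; planning intercept 22.45 and slope -0.37 per week.

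**1. The plan's own figure.** Total SD = sqrt(4.03² + 3.94²) = 5.64. With 68 per arm and a true difference of 0, SE = 5.64 × sqrt(2/68) = 0.967 and power = Φ(4/0.967 - 1.645) = 99.4%. The stated power above 95% is reproduced on these inputs. With SD 8 it would be 89.8%. The point made here does not affect the power figure.

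**2. The trigger.** 10% of 152 is 15.2, so at least 16 participants must be missing. If each is missing with probability 0.10, P(16 or more) = 0.45. The check is skipped with probability 0.55 at the planned rate. The article does not say whether the share is counted by participant, visit or end point. Counted over all four visits, 10% missing at 6 months is only (0 + 3.3 + 6.7 + 10)/4 = 5.0% with steady dropout, or (0 + 10 + 10 + 10)/4 = 7.5% if dropouts miss every post-baseline visit.

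**3. Tipping points for missing data.** If a share m of the stepped-care arm is missing and those patients score δ points worse than predicted, the difference rises by m × δ. The upper limit reaches 4 when

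δ = (4 - d - 1.645 × SE) / m, with SE = SD × sqrt(2 / (76 × (1 - m))).

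Here d is the observed difference. SE is held fixed, and only stepped care is shifted. For m = 0.10 and SD 5.64: 1.645 × SE = 1.59, so at d = 0, δ = (4 - 1.59)/0.10 = 24.1.

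| Missing | SD | d = 0 | d = 1 | d = 2 |
|---|---|---|---|---|
| 10% | 5.64 | 24.1 | 14.1 | 4.1 |
| 10% | 8 | 17.5 | 7.5 | limit already 4.25 |
| 20% | 5.64 | 11.6 | 6.6 | 1.6 |
| 20% | 8 | 8.1 | 3.1 | limit already 4.39 |

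For scale, the planning slope gives a gain of 0.37 × 16 = 5.9 points over the 16-week course. A shift of 24.1 exceeds the whole planning intercept of 22.45, and 17.5 is about three times that gain. A shift of 4.1 is less than the gain.

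**4. Excluding medication starters.** This was simulated with a true no-medication difference of 4. Starting rates, drug effect and the correlation between starting and severity are assumptions; the article gives none of them.

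| Starters, stepped care v CBT | Drug effect | Correlation | SD | Intention to treat | Starters excluded |
|---|---|---|---|---|---|
| 15% v 5% | 3 | 0.5-0.8 | 5.64 | 3.7 | 3.3-3.5 |
| 15% v 5% | 3 | 0.5-0.8 | 8 | 3.7 | 3.0-3.4 |
| 15% v 5% | 3 | 0 | 5.64 | 3.7 | 4.0 |
| 15% v 5% | 6 | 0.5 | 5.64 | 3.4 | 3.5 |
| 10% v 10% | 3 | 0.5-0.8 | 5.64 | 4.0 | 4.0 |
| 5% v 15% | 3 | 0.5-0.8 | 5.64 | 4.3 | 4.5-4.8 |

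Exclusion moves further toward noninferiority than intention to treat in the first two rows, and the other way or not at all in the rest.

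**The case against.** A reader might infer that neither sensitivity analysis can ever challenge a noninferiority claim. The documents do not support that. Excluding protocol violators is a per-protocol type of analysis, a usual companion to intention to treat in noninferiority trials, and the simulation shows that it can move the estimate away from zero. It favours noninferiority only if failing patients start medication more often under stepped care and the drug effect is not large. The article gives no such imbalance. Nonresponders in both arms are offered further face-to-face CBT before the primary end point (Nonresponders section), so failing patients have a route within the protocol other than medication. This stands.

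A reader might also set the results against what would have been seen had nobody started medication, and call the gap an error. That is a different question from the article's main analysis, which is by original allocation; choosing it is a preference, not a correction.

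Another objection is that the article condenses a full protocol in a supplement that is not shown, and that tipping-point analyses are often left to such documents. This stands in part: further analyses may exist there. The trigger and the two checks are nonetheless fixed in the article as written, and they can be judged as such.

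Finally, the imputation check does run above 10%, where missing data matter more. That is true, but even then it compares complete-case with standard imputation and still does not test worse outcomes among stepped-care dropouts.

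**Conclusion.** The concern holds in a limited form. None of the stated sensitivity analyses is reliably conservative for noninferiority. The missing-data comparison adds little to the main model, and at the planned attrition it is about as likely to be skipped as run (0.55 v 0.45, counted by participant). The exclusion analysis is a post-randomization selection whose direction depends on starting rates that the documents do not quantify.

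The practical size depends on the result. With an observed difference near 0 and 10% missing, noninferiority is safe: overturning it would need a shift of about 17 to 24 points. The gap matters mainly if the observed difference is about 1 to 2 points, if the SD is nearer 8, or if attrition is higher. At a difference of 2 with SD 5.64 and 10% missing, 4.1 points would be enough. These figures assume 76 per arm, a simple two-mean standard error and a shift in stepped care only. They do not show that the trial's conclusion will be wrong, only that the stated checks would not reveal fragility in that range.

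**What to change.** - **Remove the 10% trigger.** Run the missing-data sensitivity analysis whatever the missing rate.
- **Add delta-adjusted multiple imputation.** Worsen imputed 6-month CY-BOCS scores in the stepped care arm only, for example by 0 to 10 points. Report the delta at which the upper confidence limit reaches 4, or state that it is not reached within the range.
- **Keep the exclusion of protocol violators as supplementary only.** Its agreement with the intention-to-treat result should not be read as proof of robustness.

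Replacing scores after a medication start with the last earlier score is not recommended as the standard remedy. Table 2 shows no CY-BOCS between baseline and posttreatment, so for anyone starting during the first course that score would be the baseline one, which assumes no benefit from therapy.

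The cost is some extra programming on data already collected, with no change to conduct or sample size. The downside is a sensitivity result that may look less favourable.
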